## Abstract

**Background:**

Age-related macular degeneration (AMD) is a leading cause of vision impairment globally and demonstrates substantial variation regarding progression and clinical subtypes across populations. This paper describes the methodology of our study, designed to establish the natural history of AMD in Asian elderly and to identify predictors of progression from early signs of AMD to late AMD over a 5-year period.

**Methods:**

This prospective, longitudinal cohort study aims to recruit 1500 participants from community-based cohorts in Singapore, with a follow-up duration of 5 years. Eligible participants are adults aged 55 years or older without severe systemic illness that would preclude participation.

At baseline, demographic data and medical history will be collected, and visual acuity will be assessed. A basic imaging protocol including color fundus photography (CFP), optical coherence tomography (OCT), and OCT angiography (OCTA) will be performed. Blood samples will be collected from consenting participants. Images will be graded for early signs of AMD, defined as the presence of pathological findings on CFP, OCT, or OCTA.

Participants without early signs of AMD will undergo annual follow-up using the basic imaging protocol. Those with any pathological findings at baseline or during follow-up will undergo an enhanced imaging protocol every 6 months, including ultrawide-field fundus photography, fundus autofluorescence (FAF), OCT, and OCTA. All follow-up visits will be conducted at the Singapore Eye Research Institute (SERI).

Multimodal imaging biomarkers will be integrated with clinical, demographic, genetic, and metabolomic data to assess the relative risk of progression and identify potential predictors. The study protocol has been approved by the SingHealth Centralised Institutional Review Board.

**Discussion:**

There is a paucity of data on the progression of AMD and optimal referral thresholds, particularly in Asian populations. This community-based cohort, representative of the general population, will generate one of the largest longitudinal datasets on AMD in Asia and aims to inform future screening strategies.

Study registration number: ClinicalTrials.gov Identifier, NCT07653269.

## Introduction

Age-related macular degeneration (AMD) is a leading cause of vision impairment globally, particularly among individuals aged 50 and older, posing a significant challenge to public health [1,2]. AMD primarily affects the macula, leading to progressive central vision loss that severely impacts daily activities such as reading, driving, and recognizing faces, thereby diminishing patients’ overall quality of life [3,4]. With the global population aging rapidly, particularly in regions like Europe, North America, and Asia, the prevalence of AMD is projected to rise sharply [1]. This trend has profound implications for public health systems, demanding enhanced healthcare resources and interventions to manage the growing burden of vision impairment.

Despite its global impact, the incidence, clinical presentation, progression, and subtypes of AMD show significant variation across different populations [5,6]. Large-scale epidemiological studies, such as the Singapore Epidemiology of Eye Diseases (SEED) study and Beijing Eye Study, have shed light on these population-specific differences, highlighting unique AMD phenotypes and risk factors among Asians [6–9]. For instance, polypoidal choroidal vasculopathy (PCV), a distinct subtype of AMD, is notably more prevalent in Asian populations compared to Western populations, where traditional AMD hallmarks, such as drusen or soft drusen, are more commonly observed [9,10]. These distinctive features underscore the necessity for Asian-specific research to better understand the underlying mechanisms, risk factors, and clinical manifestations of AMD in this population.

While there is consensus regarding features that predispose to late AMD, at an individual level, risk, rate, and pattern of progression remain unpredictable; therefore, there is a need to develop effective AMD screening. This contrasts with diabetic retinopathy because the natural history is well understood, and the risk of vision loss increases sharply in those with referable DR. In AMD, this threshold is not yet established.

This paper describes the methodology of our study, designed to track retinal aging changes and understand the natural progression of AMD in a multi-ethnic Asian population. We hypothesize that there are specific high-risk features identifiable through multimodal imaging and systemic biomarkers that are associated with progression of AMD.

## Methods

### Study setting

This is a prospective, longitudinal cohort study designed to recruit participants from community cohorts in Singapore. Community cohorts were selected specifically to ensure the study cohort was generalizable to an overall population. Following the recruitment and baseline visit, over a five-year period, participants will undergo follow-up ophthalmic assessments at the Singapore Eye Research Institute (SERI).

Our specific aim is to establish the natural history of AMD in Asian elderly and to identify clinical multimodal imaging, genetic, and metabolomic predictors of progression. Progression is defined as the change from early signs of AMD to advanced AMD. Our secondary aims include: 1- define thresholds for referable early AMD suitable for community screening, 2-formulate an Asian-specific image classification system against existing AMD frameworks.

This will ultimately lead to developing personalized monitoring strategies for at-risk individuals and also inform a comprehensive and standardized community screening approach for the early detection and monitoring of AMD.

### Sample size

Previous population-based data from the Singapore Epidemiology of Eye Diseases (SEED) study reported an incidence of progression to late AMD of 0.51% among adults aged ≥40 years [10]. However, a higher progression rate is anticipated in the present study, as participants aged ≥55 years will be recruited.

The target sample size of 1,500 participants was selected to investigate progression to late AMD in an Asian community-based cohort. This sample size was determined based on feasibility and anticipated recruitment and 5-year follow-up capacity.

### Participant enrollment

Potential patients will be recruited through SingHealth Community Outreach Programme (or other smaller community-based screening projects led by our study team) and Outram Community Hospital (OCH).

The SingHealth Community Outreach Programme is an ongoing, established comprehensive initiative aimed at improving health outcomes by bringing essential healthcare services directly to the community. The current study will add an eye research component to this population health initiative.

This program, with a multi-site approach based on three main general hospitals in Singapore (Singapore General Hospital (SGH), Changi General Hospital (CGH), and Sengkang General Hospital (SKH)), focuses on accessibility and preventive care, and addresses a wide range of health concerns, including chronic diseases screening, frailty screening, and functional screening, etc. The program ensures underserved populations receive timely medical attention, health education, and referrals to help residents to keep well, get well, and live well. Through these efforts, SingHealth strives to promote healthier communities and reduce the burden of preventable diseases.

Our study adds an eye screening module (specifically for AMD), and this greatly enhances the overall impact of the SingHealth Community Outreach Programme and other community-based screening projects, further improving health outcomes.

The study team will also recruit participants from OCH. Patients at OCH are typically older adults, with an average age of 72 years old, who are usually transferred from acute hospitals such as SGH and national centers for rehabilitation and subacute care. The most common conditions are hip fracture, stroke, and rehabilitation after an acute illness. Their length of stay is an average of 28 days before returning to the community. As 95% of them return to the community, this represents an opportunity as a captive audience to perform AMD screening in this group of older adults. The hospital team and the study team will work together to identify probable participants according to the inclusion criteria:

### Inclusion criteria

Adults aged 55 years or olderWilling and able to undergo protocol-required procedures for both eyesWilling and able to provide written informed consent

### Exclusion criteria

Systemic disorders that preclude reliable clinical examination or multimodal imagingPoor compliance or severe mental illness that hinders participationPersons who are unable to give informed consent

Participants may withdraw from the study at any time without affecting their medical management or statutory rights.

### Ethical consideration

This study will be conducted in accordance with the ethical principles that have their origin in the Declaration of Helsinki and that are consistent with the Good Clinical Practice.

The final study protocol, including the Participant Information and Consent Form, has been approved by the SingHealth Centralised Institutional Review Board (CIRB) (protocol code 2025−0160)

Participants will first be identified and recruited through community screening programs. Individuals attending community screening programs will be approached by our study team (clinical research coordinators (CRC) and one of our Clinical Research Fellows) to provide information about the study and informed consent for participation. The team will emphasize that participation in the study is entirely voluntary, and declining participation will not affect the quality of healthcare they receive in any way. The risks (if any) and benefits of participation, as well as the study timeline and procedures, will be thoroughly explained. Written consent will be obtained from all participants.

### Data collection, examinations, and imaging

At baseline visit, whether in a community screening event or OCH, after gathering basic demographic data (age, gender, race), a questionnaire regarding medical history will be completed by the study team. The gathered data should include:

Past ocular history (any eye diseases or ocular surgeries),Family history of retinal diseases (with specific focus on AMD),Past medical historyWith the diagnosis date for each medical conditionPast drug history,steroid use (indication, route, dosage/frequency, start and end date),Social historySmoking (pack/year)work schedule (fixed hours or shift hours), working time and frequency,Longest stretch of undisturbed sleep (<4 hours, 4–6 hours, 6–8 hours, > 8 hours)

Presenting distance visual acuity (VA) is measured monocularly using a modified Early Treatment of Diabetic Retinopathy Study (ETDRS) LogMAR-style chart at 4 meters, with the participant wearing their current habitual distance vision correction, if any. Pinhole VA will also be measured for each eye. Results will be documented in LogMAR.

At next step, Basic imaging protocol consisting of color fundus photography (CFP), optical coherence tomography (OCT) and optical coherence tomography angiography (OCTA) all using Topcon 3D OCT-1 (Maestro 2, Topcon Inc., Tokyo, Japan, wavelength 840nm, and speed of 50,000 A-scan per second) according to the settings mentioned in Table 1 would be conducted for both eyes of each participant without pupil dilation. Scans would be repeated in the case of motion artifacts and/or image quality value (IQV) < 30.

**Table 1 pone.0355953.t001:** Detailed settings of imaging in basic protocol.

Modalities	Imaging setting
Colour Fundus Photography (CFP)	Capture one image at 45 degrees, centred on the fovea (macula), with the optic disc clearly visible in the image
Optical Coherence Tomography (OCT)	Perform 3D volume 6x6 mm (resolution of 1024 and over scan count of 4), centred on the fovea (macula)
Optical Coherence Tomography Angiography (OCTA)	Perform en-face OCTA scans with 3x3mm, (scan resolution 320x320 and over scan count of 4), centred on the fovea (macula)

Images from the Basic Protocol will be graded by research fellows within 2 months for early signs of AMD. This is defined by:

Any presence of drusen, blood, atrophy, CNV, or pigment on CFPAny changes in the outer retinal layers on OCTAny flow signal on OCTA suggestive of a CNV

All subsequent follow-up visits will occur at SERI, and the follow-up plan will be determined based on the baseline visit imaging:

If none of the early signs of AMD are present at baseline, participants will go through the Basic Protocol in the annual follow up visits till the end of the study.

If any of those signs are present at baseline or at any follow up visit, participants will be required to undergo the enhanced imaging protocol (Enhanced Protocol) during the 6 monthly follow up visits at SERI till the end of the 5-year follow-up. The participants’ flow and disposition are summarized in Fig 1.

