**Fig 1 pone.0355953.g001:**
[figure not shown]
Disposition of participants.

At follow up visits, after reviewing the medical history records and measuring height, weight, and blood pressure, distance visual acuity with or without glasses and pinhole will be measured using the LogMAR chart for both eyes of each participant.

The Basic Protocol involves community-level imaging platforms, including CFP, OCT, and OCTA, which would be performed on both eyes of each participant (without pupil dilation) using Topcon 3D OCT-1 (Maestro 2) according to the settings mentioned in Table 1.

For participants who are part of the Enhanced Protocol, the imaging modalities will include Ultra Widefield Fundus Photography, OCT, FAF, and OCTA, and will all be performed according to the setting described in Table 2.

**Table 2 pone.0355953.t002:** Detailed enhanced imaging protocol.

Imaging modality	Imaging protocols (through dilated pupils)
Optical Coherence Tomography (OCT)	Heidelberg Spectralis (Heidelberg engineering, Heidelberg, Germany) Spectral-Domain OCT, wavelength of 870 nm, A-scan speed of 70,000 scans per second, axial resolution: 3.9 µm, transverse tissue resolution: 6 µm Perform cube scan 6x6mm scan, centred on the fovea (macula), 97 horizontal B-scan, 512 A-scans per line, Automatic Real Time (ART) 7–9, and Enhanced Depth Imaging (EDI) mode on.
Optical Coherence Tomography Angiography (OCTA)	Zeiss PlexElite (PlexElite 9000, Carl Zeiss Meditec) Swept-Source OCTA, wavelength of 1050nm, A-scan speed of 100,000 scans per second Perform en-face OCTA scans with 3x3mm and 6x6mm scan, centred on the fovea (macula) DREAM OCT (Vg200, Intalight) Swept-Source OCTA, wavelength of 1070nm, A-scan and speed of 400,000 A-scans per second Perform 29 x 24 mm OCTA scan (1536 x 1280, R2), centred on the fovea (macula)
Fundus Autofluorescence (FAF)	Heidelberg Spectralis OCT Excitation blue light of 488 nm and a barrier filter beginning at 500 nm Capture two images at 30 and 50 degrees (ART > 50), centred on the fovea (macula), with the optic disc clearly visible in the image Optos (Nikon, Tokyo, Japan) Ultrawide Field FAF
Ultrawide Field Fundus Photography	Optos (Nikon, Tokyo, Japan) Capture one shot at 200 degrees of the retina, centred on the fovea (macula) and includes optic disc

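### The early-signs list overlaps with the late-AMD endpoint, and geographic atrophy present at entry cannot be classified at baseline because that visit has no FAF

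*Protocol article*

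**What the plan says.** **Starting state.** The Background of the abstract sets the aim "to identify predictors of progression from early signs of AMD to late AMD over a 5-year period", and Study setting repeats it: "Progression is defined as the change from early signs of AMD to advanced AMD". The abstract's Methods gloss the term broadly: "Images will be graded for early signs of AMD, defined as the presence of pathological findings on CFP, OCT, or OCTA". Data collection, examinations, and imaging states that "Images from the Basic Protocol will be graded by research fellows within 2 months for early signs of AMD" and gives the list itself: drusen, blood, atrophy, CNV or pigment on CFP, any outer-retinal change on OCT, and any OCTA flow that suggests CNV.

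**Use of the list.** The same section makes it the trigger for closer imaging: "If any of those signs are present at baseline or at any follow up visit", the participant moves to 6-monthly Enhanced visits.

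**Endpoint.** Grading of retinal imaging and outcomes to be measured defines late AMD as the development of MNV and/or GA. GA needs atrophy on both CFP and FAF, confirmed by cRORA on OCT, with no present or past MNV. The event is dated to the first visit at which either is found.

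**Imaging.** At baseline there is a "Basic imaging protocol consisting of color fundus photography (CFP), optical coherence tomography (OCT) and optical coherence tomography angiography (OCTA"), with no FAF. In the Enhanced Protocol, "the imaging modalities will include Ultra Widefield Fundus Photography, OCT, FAF, and OCTA".

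**Entry.** The inclusion criteria ask for "adults aged 55 years or older", ability to undergo the procedures in both eyes, and consent. Neither they nor the exclusion criteria mention existing late AMD.

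**The concern.** There are two separate problems.

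1. The label for the starting state covers findings that belong to the end state. CNV, or flow that suggests it, is an early sign in one section and the neovascular part of late AMD in another. As a trigger for Enhanced imaging the list is sensible. As the starting state of the primary aim it is not.

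2. GA that exists at entry has no way of being recognised as GA at entry under the stated definition. It can first meet that definition at a follow-up visit, where the dating rule would record it as an event.

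At stake is the primary outcome. Miscounted GA would raise the reported progression rate, mainly in the first interval, and would make signs of existing atrophy look like predictors of progression. Strengths and limitations itself warns that progressors may be few, so a small number of such eyes could carry weight.

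**Working it through.** The target of 1,500 rests on feasibility, so the article has no power or event calculation to reproduce. The main check compares definitions.

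**Step 1: overlap of states**

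| Finding | In the early-signs list? | In the late-AMD endpoint? |
|---|---|---|
| CNV on CFP, or OCTA flow suggesting it | Yes | Yes, as MNV; exudation is not required |
| Atrophy on CFP | Yes | Only with FAF and cRORA; on its own a suspected late sign |
| Blood on CFP | Yes | No; a suspected late sign |
| Drusen, pigment | Yes | No |

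The outcomes section also describes abnormal outer-retinal or sub-RPE flow without exudation as non-exudative neovascular AMD, which confirms the overlap in the first row. The footnote to Table 3 reserves the grading of haemorrhage and fundus-photograph atrophy for the late stage, which sits badly with listing them as early signs.

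**Step 2: path of an eye with GA at entry**

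1. Eligibility does not exclude it.
2. At baseline it has CFP, OCT and OCTA. Without FAF the GA definition cannot be met.
3. Atrophy on CFP, or outer-retinal change on OCT, sends the participant to Enhanced visits.
4. At the first Enhanced visit FAF becomes available. Taking the ultrawide photograph as the CFP, the definition can now be met.
5. The event is dated to that visit, which is a follow-up visit.

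For MNV the path differs. OCTA is part of baseline imaging, so MNV seen there would be dated to baseline.

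**Step 3: illustration of sensitivity**

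The number of participants with GA at entry is not in the article, so the effect is shown per miscounted participant. Sample size cites an incidence of 0.51% at age 40 or older, without a period in that sentence. Three values of true events *T*, ignoring dropout:

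- 0.51% as a cumulative figure: 1,500 × 0.0051 = 7.65
- three times that figure (my assumption, because the article expects more at 55 or older): 22.95
- 0.51% as an annual figure over 5 years: 1,500 × (1 − 0.9949^5) = 37.86

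Share of recorded events from *n* miscounted participants = n / (n + T). The share reaches 10% when n ≥ T / 9.

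| T | n = 1 | n = 3 | n for at least 10% (share of 1,500) |
|---|---|---|---|
| 7.65 | 1/8.65 = 11.6% | 3/10.65 = 28.2% | 0.85, so 1 (0.07%) |
| 22.95 | 1/23.95 = 4.2% | 3/25.95 = 11.6% | 2.55, so 3 (0.20%) |
| 37.86 | 1/38.86 = 2.6% | 3/40.86 = 7.3% | 4.21, so 5 (0.33%) |

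These are participant counts. The planned analysis is by eye, and the article gives no eye-level rate.

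**The case against.** **The endpoint is worded as incident.** It speaks of MNV developing and confines the outcome to follow-up. A discrete-time survival model normally starts from units free of the event, and an explicit risk set is commonly left to an SAP, which is not shown. This stands as evidence of intent. A reader might infer that the plan means to count prevalent late AMD as progression; nothing in the article says so. But intent does not repair the GA definition. An SAP that applied it as written could not declare any eye prevalent at a visit without FAF.

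**The reading is strict at baseline and loose later.** Missing FAF is held against the baseline visit, while ultrawide photography is accepted as CFP at Enhanced visits. The loose reading has support: the Table 3 atrophy criterion for ultrawide photographs itself refers to CFP. FAF has no such stand-in at baseline. It is fair, though, that graders already look for atrophy on CFP and outer-retinal change on OCT at baseline, so a careful analyst could see that the lesion was old. The article does not say that this information will be used. It states baseline grading only for early signs, and the detailed OCT grading that includes cRORA only for the Enhanced Protocol. Misdating is therefore possible under the text; it is not shown to be planned or likely.

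**The early-signs label is only a trigger.** As a trigger it works. The objection would succeed if Study setting did not use the same term as the start of progression.

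**Conclusion.** The point holds in two parts of different weight. The overlap of CNV with MNV is a contradiction between definitions, with no demonstrated effect on the estimate. A reader might infer that MNV present at entry is also counted as progression; baseline OCTA and the dating rule do not support that. The GA part can affect the primary outcome, because the stated definition, imaging schedule and dating rule together allow GA present at entry to enter as a first-visit event.

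The size of the bias cannot be derived. The shares above (about 3% to 12% for one miscounted participant, 7% to 28% for three) are illustrative. They depend on how the 0.51% is read and on the assumed tripling, and the largest use a rate that the article expects to be exceeded. Larger figures could be produced by assuming a prevalence of late AMD at entry, but the article gives none, and such figures would count MNV as well as GA.

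A reader might also infer that the 2-month grading limit delays care for suspected CNV. The article does not establish this: the full protocol may contain a faster route, and Participant enrollment describes an outreach programme that makes referrals.

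The wording should be corrected, and early: Timeline of the study reports 64 of 1,500 participants recruited at submission.

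**What to change.** 1. Keep the whole list as the trigger for Enhanced imaging, but split it into early signs (drusen, pigment, other outer-retinal change) and suspected late-AMD signs (CNV or abnormal flow, blood, atrophy). Use only the first group as the starting state.
2. At the baseline grading already planned, stage every eye for late AMD without knowledge of follow-up: CFP atrophy plus cRORA on OCT for GA, and OCTA with OCT for MNV.
3. Remove eyes with prevalent late AMD from the primary risk set and keep the fellow eye. Keep eyes with baseline non-exudative MNV in the planned analysis of conversion to exudative disease.
4. Flag eyes that cannot be staged at baseline, which undilated images make likely for some, and report the progression rate with and without them.

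The cost is protocol wording and a staging field in an existing grading step, with no new imaging. The GA rule at baseline would differ slightly from the one at follow-up, and somewhat fewer events would be recorded. Treating the first Enhanced visit as baseline for late-AMD status would allow the FAF-based rule throughout, but would discard true events in the first six months, so staging at entry is preferable.
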